### Randomization and allocation concealment

Participants will be randomized after baseline assessment. An independent statistician will use SPSS v23.0 (IBM Statistics, Armonk, NY) to generate the random allocation sequence, and the randomized group assignments will be stored securely in sealed envelopes by an independent researcher not involved in recruitment, evaluation, or training. After participants have provided informed consent and completed the evaluations, the envelopes will be opened and participants will be assigned to either the standardized TCPS group or one of the sham-controlled *Post Standing* groups.

#### Follow-up period

During the unsupervised follow-up period after the intervention, participants will resume their original lifestyles but will be asked to record their daily PA and stressful life events. Participants will submit these records to the researchers by email daily as follow-up. Sleep quality and quality of life will be re-evaluated using self-reported scales at the end of the four-week and eight-week follow-up periods.

## Outcome assessment

### General demographic characteristics

Baseline data collection will be collected one week prior to randomized allocation and will include general demographic characteristics including sex, age, nationality, height, weight, current disease, allergy history, medical history, family history, and medication use. Daily lifestyle factors including diet, physical activity habits, learning and living schedules, smoking and alcohol use, and participation in sports clubs and societies, as well as stressful life events, will also be recorded.

#### Efficacy outcome evaluation

Sleep quality will be measured using the PSQI and the ISI. The PSQI consists of 19 questions about sleep habits over a month measuring seven components including sleep quality, duration, and disturbances. Scores range from 0 to 21, with a cutoff of 5 indicating insomnia or clinical sleep impairment [28, 29]. The ISI is a self-reported questionnaire measuring the severity of insomnia and functional impairments in the previous month. The total score on the ISI can range from 0 to 28 points. A score of 0 to 7 indicates no clinically significant insomnia, 8 to 14 is regarded as mild insomnia, 15 to 21 is regarded as moderate insomnia, and ≥ 22 points is regarded as severe clinical insomnia [30, 31].

Quality of life will be assessed using the 36-Item Short Form Health Survey Questionnaire (SF-36), a validated 36-item questionnaire containing sections on physical functioning, role-physical, body pain, general health status, vitality, social functioning, role-emotional, mental health, and health transition. Total scores on each scale are transformed and can range from 0 to 100, where a higher score indicates better self-perceived health status [32, 33].

#### Neurophysiological assessment

A resting EEG is a graphical representation of the electrical activity of a group of brain cells. It is obtained by recording and amplifying the brain's spontaneous biopotentials from the scalp using advanced electronic equipment [24–27]. This study will use the Nuamps 40-channel EEG system and Curry 7 acquisition software (Compumedics, Charlotte, NC, United States). The sampling frequency will be set at 1000 Hz and the band-pass filter ranges from 0.01 to 100 Hz. EEG data will be preprocessed using the EEG MATLAB toolkit in MATLAB (R2012a, MathWorks, Natick, MA, United States). Power spectrum analysis will be used to measure the EEG, which quantifies the activity in different frequency bands of delta (2–4 Hz), theta (4–8 Hz), alpha1 (8–10.5 Hz), alpha2 (10.5–13 Hz), beta1 (13–20 Hz), beta2 (20–30 Hz), and gamma (30–40 Hz). The relative and absolute power levels of these frequency bands will be evaluated to assess brain activity and the basic neurophysiology of mind adjustment during TCPS. The study will also explore correlations within and between the hemispheres as well as the functional coupling between different brain areas to investigate the mechanisms underlying the effects of TCPS on insomnia.

#### Plantar pressure and biomechanical equilibrium and physical function assessments

The Footscan Balance 7.7 acquisition and recording system and Free STEP v.1.5.01 analysis software (Sensor Medica, Rome, Italy) will be used to evaluate plantar pressure and biomechanical equilibrium. A pressure sensing plate measuring 240 × 50 cm and a sampling frequency of 50 Hz will be used. The analysis will include average foot plantar pressure, peak foot plantar pressure, foot contact area, center foot plantar pressure, and biomechanical balance function index (center-of-gravity path, body swing amplitude, envelope area of posturography, and average barycentric coordinates). These measures will help to clarify the basic pathophysiology of body adjustment during TCPS [34, 35].

To measure physical function, the MP150 multiple-channel electrophysiological recording device (Upwards Teksystems Ltd., Hong Kong, China) will be utilized with a maximum sampling frequency of 400,000 points/second. The physical function measures of interest in this study include respiratory function, HRV, blood pressure, and blood oxygen saturation. Respiratory function measurements, including chest and abdominal amplitudes and movements and respiratory flow rate, will be obtained to clarify the pathophysiology of breath adjustment during TCPS [36, 37]. HRV, a sensitive and non-invasive indicator of autonomic nervous activity, will be analyzed using time-domain and frequency-domain parameters [38, 39] in combination with blood pressure [40, 41] and oxygen saturation [42, 43] measures to identify the impact of body and breath adjustments in TCPS on physical function.

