## Intervention training methods

### Standardized TCPS group (TCPS posture with abdominal breath adjustment)

Standardized TCPS group training will consist of three elements: body, breath, and mind adjustments. As seen in the standardized *TCPS* shown in Fig. 2, body adjustment consists of ball encircling training, which requires holding the arms as if embracing a tree, with the palms facing inward about two feet from the chest. The participants look forward or slightly downward and chooses a high, medium, or low stance, depending on individual fitness. The feet are planted firmly on the ground as if standing on a well stone; deep rooted and unshakable. Breath adjustment starts with a normal natural breath and gradually transitions to abdominal breathing and reverse abdominal breathing, with a slower respiratory rhythm and rate and increased volume and depth as the posture gradually lowers. Mind adjustment requires concentrating on the three circular configurations with a relaxed demeanor.

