## Sham-controlled Post Standing group I (TCPS posture with natural chest breath adjustment)

Sham-controlled *Post Standing* group I also consists of three elements: body, breath, and mind adjustment, where the body and mind adjustment training are the same as the standardized TCPS exercise. However, breath adjustment requires mainly using natural chest breathing and then only regulating breathing to make it slow, fine, and continuous.

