## Sham-controlled Post Standing group II (normal standing posture with abdominal breathing adjustment)

Sham-controlled *Post Standing* group II training again contains the three elements of body, breath, and mind adjustment. Here, body adjustment requires standing erect in a natural manner with a step sideways with the left foot such that the two feet are shoulder-width (or a little wider) and parallel with each other. The knees will be bent slightly, the hips relaxed, and the abdomen contracted. Arms will be hung loosely at the subject’s sides, with the palms facing inwards and elbows slightly bent. The fingers will be spread apart and the fingers slightly bent at the joints so that the palms are cupped and about 15 cm from the body. Breathing training is the same as standardized *TCPS*, and mind adjustment requires concentrating on the normal standing posture with a relaxed demeanor.

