## Sham-controlled Post Standing group III (normal standing posture with natural chest breath adjustment)

Sham-controlled *Post Standing* group III training has the same requirements as sham-*Post Standing* group II training, except for breathing adjustment training, which will use natural chest breathing and then only regulating breathing to make it slow, fine, and continuous.

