#### Synchronous detection procedure

Different groups of participants will be required to follow the pre-recorded guided voice instructions to practice body, breath, and mind adjustments in sequence. It should be noted that all participants at baseline will simply imitate the training practice under the pre-recorded guided voice instructions. Synchronous detection, including plantar pressure and biomechanical balance, physical function, and neurophysiological assessments, will be performed during the three-minute resting and relaxed standing state before the training practice state with self-active adjustment, the five-minute standing practice state with self-active adjustment, and the three-minute resting and relaxed standing state after the standing practice state with self-active adjustment. The stability of the instrument during the synchronous detection procedure will also be recorded.

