Studies have shown that practicing Qigong exercises increases the alpha and theta frequency band in the frontal and the parietal cortices, suggesting that Qigong stimulates and regulates brain regions related to emotional management and sensory processing through physical movements [24, 25, 27], providing a potential neurobiological basis for the beneficial effects of Qigong in addressing psychological issues. Other than frequency, functional connectivity has been shown to match the mind adjustment of Qigong exercises [27, 42]. If TCPS has a positive effect on sleep quality, this may be reflected by an increase in functional connectivity within and between hemispheres following TCPS. Conversely, prolonged periods of stress are thought to lead to the sustained and abnormal activation of the hypothalamic–pituitary–adrenal axis, which exacerbates autonomic nervous system imbalance and ultimately culminates in chronic insomnia [45–47]. In that context, examining and evaluating respiratory function, HRV, blood pressure, and oxygen saturation could provide new information on autonomic nervous system balance and physiological reactions to help explain the physiological mechanism underlying the impact of TCPS on physical function.

However, the trial also has several potential limitations. The recruitment criteria are limited to college students aged 18–26 years with insomnia. Thus, the findings of study may not be generalizable to other age groups. Additionally, the optimal intensity and timing of TCPS remain unknown, but we believe that the TCPS scheme used in this trial will provide information for any further optimization studies. Despite these limitations, this trial represents an important milestone in the development of new therapeutic approaches for insomnia and will be easily implementable for college students with insomnia.

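### HRV recorded during trained breathing cannot by itself support an autonomic conclusion for TCPS against sham I or III, or for change over time within TCPS

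*Protocol article*

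**What the plan says.** All references are to the Protocol article.

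- **Meaning given to HRV.** The section on plantar pressure and physical function states: "HRV, a sensitive and non-invasive indicator of autonomic nervous activity, will be analyzed using time-domain and frequency-domain parameters". The Discussion adds that respiratory function, HRV, blood pressure and oxygen saturation "could provide new information on autonomic nervous system balance".
- **Breathing trained in each arm.** In the TCPS arm, breathing passes from natural to abdominal "with a slower respiratory rhythm and rate and increased volume and depth as the posture gradually lowers". For sham II, "Breathing training is the same as standardized" TCPS. In sham I, "breath adjustment requires mainly using natural chest breathing and then only regulating breathing to make it slow, fine, and continuous". Sham III differs from sham II only in its breathing, "which will use natural chest breathing and then only regulating breathing to make it slow, fine, and continuous".
- **When HRV is recorded.** The synchronous detection procedure has three windows: "the three-minute resting and relaxed standing state before the training practice state with self-active adjustment", then "the five-minute standing practice state with self-active adjustment", then three more minutes of relaxed standing. At baseline, participants only imitate the practice.
- **Respiration.** Chest and abdominal movement and airflow are measured with the same system. Their stated purpose is to characterise breath adjustment.
- **Analysis.** The statistical section names a group × time repeated-measures ANOVA, for TCPS against the sham groups and for change within TCPS. It does not separate rest from practice windows for HRV.

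**The concern.** Heart rate oscillates with breathing. A fixed high-frequency band captures that oscillation only while the breathing rate stays inside the band. If the rate drops below the lower limit, the same oscillation is counted as low-frequency power, although nothing in autonomic control has changed. Deeper breathing may also enlarge the oscillation, which would move time-domain measures.

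Here the intervention trains breathing itself, and one of the three recording windows is taken while that breathing is performed. A difference between TCPS and a chest-breathing sham, or a change within TCPS from the imitated baseline practice to the trained practice at 8 or 14 weeks, could be a shift of breathing frequency across a band limit. Read as the article proposes, it would be reported as evidence of altered autonomic balance, which the Discussion links to chronic insomnia. At stake is a mechanistic claim on a secondary outcome.

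**Working it through.** The article reports no HRV figure to reproduce, so the check asks what fixed-band HRV does when only the breathing rate changes.

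**Inputs from the article.** 25 per arm with 20% attrition: 25 × (1 − 0.20) = 20 per arm. Windows of 180 s (rest) and 300 s (practice).

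**Assumptions, not in the article.** LF 0.04-0.15 Hz and HF 0.15-0.40 Hz; respiratory oscillation of amplitude 40 ms; slow oscillation near 0.095 Hz of amplitude 20 ms; white noise of SD 10 ms, sampled at 4 Hz; all breathing rates.

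**Step 1, the band limit.** 0.15 Hz × 60 = 9 breaths/min.

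**Step 2, power by band.** A sinusoid of amplitude A has power A²/2, so respiratory power is 40²/2 = 800 ms² and slow power is 20²/2 = 200 ms². Noise power of 10² = 100 ms² spread over 0-2 Hz is 50 ms² per Hz. That gives 0.11 × 50 = 5.5 in LF and 0.25 × 50 = 12.5 in HF.

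- Breathing above the limit: LF = 205.5, HF = 812.5, LF/HF = 0.25.
- Breathing below the limit: LF = 1005.5, HF = 12.5, LF/HF = 80.
- SDNN in both cases: √(800 + 200 + 100) = 33.2 ms.

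**Step 3, simulation** (300 series per setting, Welch spectra, 300 s window; 180 s gives the same picture):

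| Breaths/min | LF (ms²) | HF (ms²) | Median LF/HF | SDNN (ms) |
|---|---|---|---|---|
| 15 | 205 | 812 | 0.25 | 33.2 |
| 10 | 205 | 810 | 0.25 | 33.1 |
| 9 | 340 | 676 | 0.50 | 33.2 |
| 8 | 1005 | 13 | 76 | 33.2 |
| 6 | 1003 | 13 | 78 | 33.0 |

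The effect is a step at the limit. From 18 down to 10 breaths/min nothing moves.

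**Step 4, time domain.** With fixed respiratory amplitude SDNN stays at about 33 ms. It rises, from 33 ms at 15/min to 57 ms at 6/min, only if the oscillation is also assumed to grow as breathing slows (low-pass response).

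**Step 5, a two-arm comparison.** A t-test on log(LF/HF), 20 per arm, breathing-rate SD 2/min, oscillation amplitudes varying between people but with the same distribution in both arms, 200 simulated trials per row. This simplifies the planned ANOVA. The share of each arm below 9/min is Φ((9 − mean)/2).

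| Mean rates (per min) | Share below 9/min | Trials with p < 0.05 |
|---|---|---|
| 12 v 12 | 7% v 7% | 3.5% |
| 10 v 12 | 31% v 7% | 45% |
| 8 v 10 | 69% v 31% | 74% |
| 8 v 12 | 69% v 7% | 100% |

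Equal rates give about the nominal error. Unequal rates near the limit give frequent differences with no autonomic difference behind them.

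**Step 6, which contrasts are exposed.** TCPS and sham II share the breathing instruction. Shams I and III are also told to breathe slowly, but not to deepen. Exposure is therefore greatest for TCPS against sham I or III, and only to the extent that achieved rates and depths differ. Change within TCPS is exposed whatever the shams do, because the baseline practice recording is an untrained imitation. The relaxed-standing windows ask for no practice and are less exposed, though trained breathing may carry over.

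**The case against.** **Breathing is the intended route.** Hypothesis (ii) expects HRV to change because of body and breath adjustments, and the physical-function section gives the same purpose. This stands: an HRV change produced by trained breathing is consistent with the hypothesis as written. A reader might infer that the hypothesis is unsound or that any HRV finding would be an artefact; the article does not support either. What remains is the further step from an HRV change to autonomic activity or balance, which the article does take, though in hedged terms in the Discussion.

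**The article names no bands and no LF/HF ratio.** True. A reader might infer that the trial will report a rise in LF/HF as sympathetic activation; nothing in the text says so. Nor does silence show that the respiratory signal will go unused: a fuller plan may set bands or a respiratory correction. The point therefore concerns the stated interpretation, not missing signal-processing detail.

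**The design already separates posture from breathing.** Largely right for TCPS against sham II. It does not help the contrasts with shams I and III, or the within-TCPS comparison.

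**Adjusting for breathing would remove the effect sought.** Also right. Breathing rate arises after randomisation and is a proposed mediator, so an adjusted result should not become the main one.

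**Conclusion.** The concern holds in a limited form. In the practice window, frequency-domain HRV contrasts of TCPS with sham I or III, and changes over time within TCPS, cannot by themselves support a statement about autonomic activity. TCPS against sham II is less exposed.

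The possible distortion of LF/HF is very large, roughly 300-fold in the idealised case (76 / 0.25 = 304), but only for participants whose breathing falls below about 9 breaths/min, and only with conventional fixed bands. Neither the bands nor the breathing rates are in the article, so the size in this trial is unknown and could be nil if everyone stays above the limit. An effect on time-domain measures needs the further assumption in step 4.

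It would go too far to conclude that the whole HRV analysis is invalid or that all between-group inference must move to the rest windows. HRV is a secondary mechanism outcome. The PSQI efficacy analysis, the EEG outcome and the sample size are untouched. The change is still worth making, because it is cheap and guards against a misleading mechanistic conclusion.

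**What to change.** In the physical-function and statistical analysis sections:

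1. Keep the planned HRV analyses, but describe practice-window HRV as a cardiorespiratory response to the breathing instruction.
2. Rest any statement about autonomic balance on the relaxed-standing window before practice, and note that trained breathing may carry over into it.
3. Report breathing rate and depth by arm and window from the respiratory signal already recorded, so that readers can see how many recordings fall below the band limit.
4. Add a sensitivity analysis with the respiratory band centred on each recording's own breathing frequency.
5. Label any result adjusted for breathing rate as supplementary, because rate is a post-randomisation mediator.

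Cost: wording and a little more signal processing, with no new measurement. Practice-window HRV loses its stand-alone autonomic interpretation, and autonomic statements then describe the state at rest before practice, not the state during TCPS.

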#### Synchronous detection procedure

Different groups of participants will be required to follow the pre-recorded guided voice instructions to practice body, breath, and mind adjustments in sequence. It should be noted that all participants at baseline will simply imitate the training practice under the pre-recorded guided voice instructions. Synchronous detection, including plantar pressure and biomechanical balance, physical function, and neurophysiological assessments, will be performed during the three-minute resting and relaxed standing state before the training practice state with self-active adjustment, the five-minute standing practice state with self-active adjustment, and the three-minute resting and relaxed standing state after the standing practice state with self-active adjustment. The stability of the instrument during the synchronous detection procedure will also be recorded.

#### Reporting adverse events and safety evaluations

No adverse events have been reported during our preliminary investigations. However, if any adverse events occur during the study (such as headaches, dizziness, chest tightness, palpitations, muscle soreness, or other physical discomfort), whether related to the study or not, they will be recorded in detail, including the timing, severity, and management. If any serious adverse events occur, the researchers will immediately report them to the medical ethics committee, who will decide if the participant needs to withdraw from the study. The relationship between serious adverse events and intervention training will also be analyzed.

#### Data management and monitoring

Two professional research assistants will conduct quality control of data collection and be responsible for entering their files into the same database, crosschecking them for data accuracy, and storing it with password protection.

#### Statistical analysis

We will use IBM SPSS Statistics 25.0 (IBM Statistics, Armonk, NY) for statistical analysis, with a significance threshold of 0.05 and 95% confidence intervals for all estimates. Categorical variables will be reported as frequencies or percentages, while continuous variables will be described using mean ± standard deviation for normally distributed data and median [interquartile range (IQR)] for non-normally distributed data. We will conduct intention-to-treat (ITT) and per-protocol (PP) analyses for all outcomes. If ITT and PP results are consistent, we will consider them reliable; otherwise, ITT results will be preferred. For missing data, we will use multiple imputation and last observation carried forward analysis. Baseline demographic characteristics will be compared between groups using analysis of variance (ANOVA), non-parametric Wilcoxon signed rank, or chi-squared tests. Adjusted analysis with multiple linear regression or logistic regression will be performed if potential confounding factors are present. Repeated-measures ANOVA (group × time) will be conducted to compare outcome measures between the standardized TCPS and sham-controlled *Post Standing* groups and within the standardized TCPS group at different assessment time points. Safety will be assessed by recording and reporting adverse events for each group. A chi-squared or Fisher's exact test will be used to compare frequency differences in adverse events between groups, and severe adverse events will be described in detail. Logistic regression and linear mixed-effects models will be employed to explore factors affecting adherence and feasibility, adjusted for confounders. Adherence-related data will be obtained from training self-evaluation logs and sign-in sheets.

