### Sample size estimation

Sample size calculations were performed a priori using G-Power Software (v3.1.9.7, Germany). Due to limited previous studies on the use of *Post Standing* or other Qigong exercises in participants with insomnia, the effect size calculation was based on the best available data regarding the hypothesized change in PSQI score found in the literature. The PSQI effect size ranged from 0.31 to 0.83, so we adopted a conservative estimate of 0.31 for our calculation [44]. An F-test ANOVA (repeated measures, within-between interaction) was used for four groups and three measurements. The desired power was set at 80%, with a two-sided α error probability of 0.05. This resulted in a required sample size of 80 participants. Considering a potential attrition rate of 20%, we aim to recruit a minimum of 100 participants for this study. To allocate an equal number of participants to each arm (1:1:1:1), a minimum of 25 participants per arm is necessary.

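### Multiple imputation and last observation carried forward are both planned with neither named as primary; an LOCF-based ITT comparison would be biased if scores improve over time and dropout is uneven

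*Protocol article*

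**What the plan says.** All of the following is in the protocol article; no separate analysis plan is at hand.

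- **Missing data** (Statistical analysis): "For missing data, we will use multiple imputation and last observation carried forward analysis". No order, no sensitivity role, no split by outcome, and no rule for the case where the two disagree.
- **Analysis sets** (same section): "We will conduct intention-to-treat (ITT) and per-protocol (PP) analyses for all outcomes". A ranking follows: "If ITT and PP results are consistent, we will consider them reliable; otherwise, ITT results will be preferred".
- **Main model** (same section): "Repeated-measures ANOVA (group × time) will be conducted to compare outcome measures", with group by time as the term of interest.
- **Expected loss** (Sample size estimation): "Considering a potential attrition rate of 20%, we aim to recruit a minimum of 100 participants for this study". The 20% is not split by arm.
- **Visits** (Study setting and procedure; Table 1): PSQI at baseline and weeks 8 and 14, then at weeks 18 and 22. The first post-baseline score is therefore at week 8.

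**The concern.** The two methods rest on different assumptions and can give different answers. The only ranking in the section, ITT over per-protocol, concerns analysis sets. It does not help here, because the preferred ITT result could itself come from either method. As written, the primary ITT result is not uniquely defined before the data are seen.

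LOCF is also a poor candidate in this design. Anyone who stops in the first seven weeks contributes the baseline PSQI as the week-14 value. If participants generally improve, for whatever reason, LOCF denies that improvement to those who leave, so the arm with more dropout looks worse than it is. As a single imputation it also enters the filled-in values as though they had been measured, which makes standard errors too small.

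Uneven dropout is plausible on two grounds. The TCPS posture has the arms held up, whereas sham groups II and III stand naturally with the arms hanging, so physical demand may differ in those two comparisons. And with 25 per arm, appreciable imbalance arises by chance alone.

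**Working it through.** **1. The plan's own figures.** The calculation uses four groups, three measurements, effect size 0.31, α 0.05 and power 80%. A noncentral-F calculation for the within-between interaction gives a minimum N of 80 (power 0.813) under the effect-size convention that G*Power labels as in SPSS; the article does not say which convention was used. Attrition: 80 / (1 − 0.20) = 100, or 25 per arm. Both stated figures reproduce, and the planned loss is about 20 of 100 participants.

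**2. Formula for LOCF.** Let d be the dropout proportion in an arm, s the share of dropouts leaving before week 8, F8 the mean fall in PSQI by week 8 and F14 the mean fall by week 14. Take dropout as unrelated to outcome. The mean fall that LOCF shows at week 14 is

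(1 − d) × F14 + d × [s × 0 + (1 − s) × F8].

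**3. Inputs, all assumed.** The article gives no trajectory and no dropout by arm. I take F14 = 3 points in every arm, so the true difference is zero. Dropout is 28% in TCPS and 12% in a sham arm, that is 7 and 3 of 25. With 5 of 25 in each of the other two arms the total is 20 of 100, matching the planned rate.

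**4. Half of dropouts leave before week 8, half the fall achieved by then** (s = 0.5, F8 = 1.5):
- TCPS: 0.72 × 3 + 0.28 × 0.75 = 2.16 + 0.21 = 2.37
- Sham: 0.88 × 3 + 0.12 × 0.75 = 2.64 + 0.09 = 2.73
- Spurious difference: 2.73 − 2.37 = **0.36 points** against TCPS

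**5. All dropouts leave before week 8** (s = 1):
- TCPS: 0.72 × 3 = 2.16; sham: 0.88 × 3 = 2.64
- Spurious difference: **0.48 points** against TCPS
- With a 2-point common fall instead: 0.16 × 2 = 0.32 points

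**6. Other cases.**
- Equal dropout of 20%, no true difference: both arms show the same fall, so the bias is **zero**.
- Dropout reversed (12% in TCPS, 28% in sham): same size, now in favour of TCPS.
- Equal 20% dropout with an assumed true difference of 0.93 points (0.31 × an assumed SD of 3), using the timing in step 4: TCPS falls of 1.97 and 3.93 give 0.8 × 3.93 + 0.1 × 1.97 = 3.34; sham gives 0.8 × 3 + 0.1 × 1.5 = 2.55. LOCF shows 0.79 instead of 0.93.

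**7. Imbalance by chance.** If every arm has a true dropout of 20%, the exact binomial probability that two given arms of 25 differ by at least 4 dropouts (as 7 versus 3 does) is about 21%.

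**The case against.** The strongest reply is that this is one condensed paragraph of a journal article, and the ranking of methods may stand in an analysis plan that is not shown. Naming two methods is not a contradiction; the sentence is compatible with one primary method and one check. That has force against any claim that the article formally gives the two equal standing: it states no standing at all. It does not remove the point, because the article itself commits to LOCF in an unspecified role while ranking the analysis sets in the same section.

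Four stronger readings are tempting and are not supported.

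- *The ITT result will be biased.* Only if the LOCF version is the one reported. Multiple imputation does not carry this bias under missing at random. The statistician is also to work with coded groups, which limits selection by favoured arm, though it does not remove it.
- *Dropout will be heavier under TCPS because the posture is harder.* Sham group I uses the same body and mind adjustment, so the argument does not reach that comparison. TCPS participants may also choose a stance height to suit their fitness, and groups II and III are not wholly passive either.
- *All arms are expected to improve.* The article does not say so. Its hypothesis is about TCPS relative to sham, and coaches are to tell participants only that every form of training may help. Entry on elevated PSQI and Insomnia Severity Index (ISI) scores makes some common fall likely, but it remains an assumption.
- *Repeated-measures ANOVA will discard everyone with a missed visit.* That describes an analysis without imputation; this plan fills values in.

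**Conclusion.** The point stands as a should-fix matter of analysis choice. The method behind the primary ITT result is not fixed, and one of the two candidates is a single imputation that understates uncertainty and can distort the group comparison.

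The plausible distortion is about 0.36 to 0.48 PSQI points, given a 3-point common fall and 28% versus 12% dropout. The upper figure needs every dropout to leave before week 8. The bias always runs against the arm with more dropout when scores improve, so its direction for TCPS is not known in advance, and it vanishes under the null when dropout is equal. For scale, if 0.31 is read in SD units with an SD of 3, the planning effect is 0.93 points, so the distortion would be roughly 40% to 50% of it (0.36 / 0.93 = 0.39; 0.48 / 0.93 = 0.52). The SD, the trajectory, the timing and the split by arm are all assumptions. The lack of a named primary method does not depend on them.

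**What to change.** In the Statistical analysis section, name one primary missing-at-random approach for the PSQI ITT analysis. Either of these would do:

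- a linear mixed model for repeated measures fitted to all observed data, or
- the multiple imputation already planned.

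Then drop LOCF, or keep it only as a labelled sensitivity analysis that cannot replace the primary result.

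The cost is a minor rewording of the analysis text, made before unblinding. The required sample size stays at 80, or 100 after attrition, and no visit or measurement changes.
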